**Methods and analysis:**

A total of 100 jaundiced newborns aged two weeks or younger will be included in this randomized, single-blind (the parents knew, but the neonatologists did not know), single-center controlled trial to receive either 10^9^ colony-forming units of AB-GG, Bb-12, M-16V, a combination of the three probiotics with blue-light phototherapy, or blue-light phototherapy alone. The experimental group will be treated with oral probiotics once daily for 30 days, while the control group will receive only blue-light phototherapy. The follow-up duration will last 30 days. The primary outcomes include changes in gut microbiota, metabolomics, and the incidence of phototherapy side effects, assessed after each phototherapy session, as well as on days 10, 20, and 30.

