### Eligibility criteria

(1)Inclusion criteria: (1) Jaundice index: According to the American Academy of Pediatrics phototherapy guidelines, the jaundice index reaches the phototherapy threshold; (2) age ≤2 weeks; (3) Term infants with 37 weeks ≤ gestational age < 42 weeks and 2,500 g ≤ birth weight < 4,000 g; (4) No prior use of antibiotics or ecological agents before specimen collection; (5) Healthy mothers during pregnancy, with no history of special drug use, and no intake of antibiotics or microecological agents before, during, or after childbirth; (6) Enrolled infants were exclusively breastfed, exclusively formula-fed, or mixed-fed before admission; (7) All enrolled infants had neonatal pathological jaundice as defined by “Practical Neonatology” and required hospital admission solely for phototherapy; (8) Informed consent provided voluntarily.(2)Exclusion criteria: (1) Gestational age <37 weeks or ≥42 weeks; (2) bilirubin levels reaching the exchange blood transfusion standard or elevated direct bilirubin; (3) complications with pneumonia, septicemia, or other diseases; (4) patients with severe immunodeficiency diseases; (5) those with inherited metabolic diseases; (6) congenital biliary malformations or other organ malformations; (7) drug allergies; (8) situations that may warrant exclusion as determined by the researcher, such as a guardian with mental illness or frequent changes in living or working environments, which may result in loss of follow-up.(3)Elimination criteria: (1) Those refusing the use of their newborn information and their stools and blood; (2) During the treatment process, other drugs might be needed to be added because of other diseases, such as the use of antibiotics and micro-ecological agents.(4)Criteria for withdrawal from the study: (1) participants who suddenly refuse stool and blood collection and request to withdraw from the study; (2) severe gastrointestinal symptoms, such as intense vomiting, diarrhea, or abdominal distension, and other adverse events that significantly affect the treatment process during the probiotics intervention; (3) neonates requiring exchange blood transfusion due to the continued worsening of jaundice after active phototherapy; (4) neonates lost to follow-up, unreachable, or unable to return to the study center for visits.

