(1)Definition of adverse events: In this clinical trial, adverse events are defined as severe vomiting, diarrhea, disruption of normal eating habits, or significant necrotizing enterocolitis occurring during the use of probiotics. Additionally, an adverse event is defined as a severe increase in jaundice value that reaches the index for exchange transfusion.(2)Diagnostic criteria of adverse events: (1) Severe vomiting:vomit 5 or more times per day for 2 or more days; (2) Diarrhea 8 or more times per day for 2 or more days; (3) Necrotizing enterocolitis:Neonatal necrotizing enterocolitis is diagnosed according to the Clinical guidelines for the diagnosis and treatment of neonatal necrotizing enterocolitis (2020); (4) According to the Clinical Practice Guideline Revision: Management of Hyperbilirubinemia in the Newborn Infant 35 or More Weeks of Gestation, exchange transfusion criteria have been met.(3)Degree of adverse events: (1) Mild: Neonates can tolerate the event, which does not affect treatment, does not require special treatment, and has no impact on the neonates' health. (2) Moderate: Neonates find the event unbearable, affecting the treatment and having a direct impact on their health. (3) Severe: The event endangers the neonate's life, potentially causing death or disability, and requires immediate emergency treatment.(4)Possibility of adverse events: Although every bacterium in the probiotic combination used in this study is approved by the National Ministry of Health as safe and reliable, adverse events cannot be completely ruled out. However, the probability of adverse events is expected to be low(5)Treatment of adverse events, follow-up methods, and time: In case of adverse events, the incident will be promptly reported, and the clinical trial for the affected neonate will be terminated in a timely manner to prioritize their safety. The patient's stool and gastrointestinal symptoms will be monitored daily, and plain abdominal radiographs will be performed as needed. For patients with severe jaundice requiring exchange transfusion, exchange transfusion therapy will be immediately initiated, as well as monitoring jaundice dynamically and conducting brain MRI and brainstem auditory evoked potential assessments. Post-discharge follow-up will be conducted, selecting various follow-up methods based on the situation. If a neonate with jaundice experiences adverse events after taking probiotics or if such events are suspected to be related to the probiotic administration, strict records should be maintained, the adverse event form should be completed, and the main responsible personnel and the Clinical Research Center of the East Hospital of Shanghai Sixth People's Hospital will be informed within 24 h according to the established process. The ethics committee will decide whether to halt the trial immediately.(6)Risk prevention of adverse events: All adverse events occurring during treatment will be graded according to severity and documented in detail using a CRF (Case Report Form). The potential relationship between adverse events and probiotics will be analyzed. If severe adverse reactions occur, the trial should be stopped immediately. Serious adverse events must be reported in strict accordance with the relevant provisions of GCP (Good Clinical Practice). The group will not receive any drugs or additional probiotics in their milk.

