### Endpoints

(1)Primary endpoint: significant reduction in the incidence of clinical side effects (i.e., diarrhea, rash, fever, vomiting, convulsions, feeding intolerance, etc.).(2)Secondary endpoints: after the addition of probiotics, the intestinal flora will be maintained in a stable state after phototherapy, and the changes in metabolic indicators; changes in jaundice (i.e., serum bilirubin, bile acid and transcutaneous bilirubin data), feeding status, changes in urine volume and weight, and vital signs during phototherapy

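### Gastrointestinal and feeding events that overlap the primary endpoint remove an infant from the trial, not only from the product, under two rules with different triggers

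*Protocol article*

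**What the plan says.** Two places in the protocol article decide what happens to an infant with a gastrointestinal or feeding event.

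- **Eligibility criteria, part 4.** Under the title "Criteria for withdrawal from the study", item 2 lists "severe gastrointestinal symptoms, such as intense vomiting, diarrhea, or abdominal distension, and other adverse events that significantly affect the treatment process". It gives no counts or duration.
- **Interventions, adverse event observation.** Item 1 defines the events: severe vomiting, diarrhea, "disruption of normal eating habits, or significant necrotizing enterocolitis occurring during the use of probiotics", and jaundice that reaches the exchange-transfusion level. Item 2 sets thresholds of at least 5 vomits or at least 8 episodes of diarrhea per day, each for 2 or more days. It refers to guidelines for necrotizing enterocolitis and exchange transfusion, and gives no criterion for disrupted eating. Item 3 grades events, beginning with "Mild: Neonates can tolerate the event, which does not affect treatment, does not require special treatment". Item 5 then states that for an adverse event "the clinical trial for the affected neonate will be terminated in a timely manner to prioritize their safety".

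The primary endpoint under Endpoints is "significant reduction in the incidence of clinical side effects (i.e., diarrhea, rash, fever, vomiting, convulsions, feeding intolerance, etc". The abstract (Methods and analysis) lists "the incidence of phototherapy side effects, assessed after each phototherapy session, as well as on days 10, 20, and 30". Study procedure says in general terms that every subject is followed for one month, with stool and data collection at the day 10, 20 and 30 clinic visits.

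**The concern.** Both rules end participation. Neither provides for stopping the probiotic while the scheduled assessments continue. The trigger events are of the same kind as the outcome (vomiting, diarrhea, feeding problems), so the infants who lose their late assessments are selected on outcome. A later analysis plan can choose how to handle missing data, but it cannot recover visits and samples that the protocol tells staff not to collect.

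The two rules also disagree. An infant with an event graded mild stays under the withdrawal criteria, which require severe symptoms or a significant effect on treatment. The same infant leaves under item 5, which adds no grade to the definition of an event. Disrupted eating is a trigger without a criterion.

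There is also a possible difference between arms. Item 1 ties the gastrointestinal and feeding events to the period of probiotic use, and the control arm takes none. Read literally, only infants in the four probiotic arms could be removed for them.

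**Working it through.** **The plan's own figure.** Sample size gives 47% versus 10%, type I error 0.05, power 0.8 and 20 per group. The two-proportion formula with unpooled variance, two-sided and without the stated margin, gives (1.960 + 0.842)² × (0.47 × 0.53 + 0.10 × 0.90) / 0.37² = 19.44, which rounds up to 20. No allowance for exits is shown, and each exit is 1/20 = 5% of an arm.

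**Comparison of the triggers**

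| Event | Withdrawal criteria | Adverse event rule |
|---|---|---|
| Vomiting, diarrhea | severe; no counts | daily counts for 2 or more days |
| Abdominal distension | named | not named |
| Necrotizing enterocolitis | not named | named, by guideline |
| Disrupted eating | only if treatment is significantly affected | any; no criterion |
| Event graded mild | stays | leaves, read literally |

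For vomiting, diarrhea and necrotizing enterocolitis the two rules largely coincide in practice, because the thresholds are high. The real gaps are events graded mild and disrupted eating.

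**Amount of data lost.** The article gives no exit rate. I assume w = 5% or 10%; the latter is the digestive side-effect rate planned on probiotics.
- Infants: 0.05 × 100 = 5, or 0.10 × 100 = 10.
- Late visits: 5 × 3 = 15, or 10 × 3 = 30, of 300. These are upper limits, reached if every exit precedes day 10.
- Standard error if all arms leave alike: √(20/19) = 1.026 or √(20/18) = 1.054, a rise of 2.6% or 5.4%.

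**Understatement of late side effects.** The true rate minus the rate among stayers is w × (leavers' rate − stayers' rate). With an assumed gap of 30 to 50 points this is 1.5 to 2.5 points at w = 5% and 3 to 5 points at w = 10%.

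**Common rule, probiotics working as planned.** Let f be the assumed share of digestive side effects that reach the trigger, and apply 10% to every probiotic arm (assumed).
- f = 0.10: 0.47 × 0.10 × 20 = 0.94 controls leave, and 0.10 × 0.10 × 20 = 0.2 infants per probiotic arm.
- f = 0.25: 2.35 and 0.5.
- The late difference shrinks by 0.37 × f × 30 to 50 points, which is 1.1 to 1.9 (f = 0.10) or 2.8 to 4.6 (f = 0.25). This works against probiotics.

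**False-positive check.** This is a simulation of the Mann-Whitney test, which the article names for group comparisons: 40,000 runs, 20 per arm, no true effect, two-sided 0.05. In each arm w × 20 infants are 0.5 or 1 SD worse (assumed) on a generic continuous late measure. The result is the share significant in favour of probiotics.

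| Scenario | w = 5% | w = 10% |
|---|---|---|
| Leavers drop out in both arms | 2.3%, 2.2% | 2.4%, 2.5% |
| Only probiotic infants leave | 2.7%, 2.9% | 3.2%, 4.1% |

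Each cell gives the 0.5 SD result, then the 1 SD result. With no symptomatic infants the share is 2.4% to 2.5%.

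**The case against.** The strongest reply is that the primary endpoint is an incidence. An infant who meets a trigger has already had a qualifying event, so any-event status is unaffected if that event is counted. This stands. A larger distortion of the primary comparison would require leavers to be dropped from the analysis as well, which the article does not say.

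Second, the infant is not lost to observation. Item 5 keeps daily stool and gastrointestinal monitoring and some post-discharge contact, Monitoring follows adverse events until they resolve or stabilize, and Study procedure follows every subject for a month. This stands in part: the first two are safety care, and the third is a general statement. None says that a terminated infant keeps the day 10, 20 and 30 side-effect and stool assessments. If that is the intention, the termination wording contradicts it.

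Third, the difference between arms is only one reading. The withdrawal criteria can be read as neutral, item 6 grades all adverse events during treatment, and Blinding keeps the neonatologists unaware of allocation. This stands, and I treat the asymmetry as possible only.

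Fourth, events should be few: item 4 says that "the probability of adverse events is expected to be low". The 10% exit rate is the planned rate of any digestive side effect, not of events at the trigger thresholds, so it is generous. This also stands and limits the size.

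Finally, ending participation is a cautious choice for a sick newborn. Stopping the product gives the same protection from it; ending scheduled assessments adds none.

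**Conclusion.** The point holds. As written, the protocol removes infants from the trial for events related to the outcome, under two triggers that do not match, and does not secure their day 10 to day 30 assessments. The loss concerns later side effects and later samples.

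The effect is unknown and probably small. Under a rule applied alike in all arms, late side effects are understated in every arm and no false benefit is expected; if probiotics work as planned, late differences shrink. A bias favouring probiotics arises only under the literal, arm-specific reading, and even then it is modest in the scenarios examined. All exit rates, gaps and shifts are assumptions. I claim no direction for microbiota or metabolites. The protocol should be changed because the remedy is cheap and the lost data cannot be recovered later, not because the trial's main result is shown to be in danger.

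**What to change.** Put one trigger in both Eligibility criteria (part 4, item 2) and Interventions (adverse event observation, item 5), worded identically for all five arms including control. The investigators should set its clinical threshold and add a criterion for disrupted feeding. State that meeting the trigger stops the assigned product only, and that the infant keeps the scheduled day 10, 20 and 30 assessments unless the parents withdraw consent.

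The cost is protocol wording; the visits and samples are already planned. Because recruitment began in June 2021, the change may need an ethics amendment. The downside is that some late samples will come from infants off product. The separate rules on added antibiotics or other drugs and on exchange transfusion are not altered by this change.

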
### Study procedure

Figure 1 illustrates the details of the research procedure. Parents will continue to receive information about the study for 30 days after enrollment when the newborn has confirmed that neonatal hyperbilirubinemia has met the criteria for phototherapy for the appropriate age, including during their regular follow-up visits to the hyperbilirubinemia clinic. Pediatricians participating in the study will sign written informed consent with parents. Subjects will be randomly assigned to receive AB-GG combined with phototherapy, Bb-12 combined with phototherapy, M-16V combined with phototherapy, all of the above probiotics combined with phototherapy, or phototherapy alone, following the method of a digital randomization list. The probiotic dose is 10^9^ colony-forming units (5 drops) administered orally once daily for 1 month. All subjects will be followed up for 1 month after the start of the intervention. Data and specimen collection on days 10, 20, and 30 will be completed during the outpatient follow-up for hyperbilirubinemia.

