### Interventions

(1)Interventions: Neonates will be placed in a blue light treatment box (Ningbo David Medical Device Co., LTD, XHZ model) with the temperature set at 30°C and relative humidity at 55%. Phototherapy eye masks (Foshan Forman Medical Technology Co., Ltd., Yuesun Mechanical Equipment No. 20160015) and phototherapy diapers (Foshan Baojusheng Medical Equipment Co., Ltd., GB/T33280) will be used to cover the eyes and perineum. The treatment will involve LED blue light continuous irradiation with a wavelength of 425–475 nm. All neonates will undergo continuous phototherapy for 12 h, rest for 6–8 h, and then receive another 12 h of continuous phototherapy. The decision to continue with the next 12 h treatment session will depend on the changes in the neonate's jaundice condition.(2)Study drug and specifications: The patented probiotic combination (contains Bifidobacterium breve 10^9^, Lactobacillus rhamnosus 10^9^ and Bifidobacterium animalis 10^9^ per package) (invention patent, 202,010,414,426.7) will be added to the corresponding groups. The aforementioned drugs are freeze-dried powder, stored at room temperature, with a 30-month shelf life, and manufactured by China Taiwan Jinqiao Biological Co., Ltd. Probiotics intervention: the probiotics will be administered to jaundiced newborns requiring phototherapy. The experimental group will receive the corresponding daily probiotics during phototherapy. The probiotics will be mixed into the milk and consumed once a day, with a treatment course lasting for one month. Clinical study criteria will be controlled to determine the termination of the study.(3)Criteria for stopping the clinical study: (1) occurrence of serious adverse events occur that may be related to the use of probiotics; (2) if the planned interim analysis achieves the expected difference in efficacy and the intervention is observed to be significantly more effective in the trial group compared to the control group.(4)Adverse event observation

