### Allocation concealment

Based on the randomization table, each enrolled subject will be assigned a serial number in order, which will correspond to one of the following groups: C0 (phototherapy only), T1 (M-16V combined with phototherapy), T2 (Bb-12 combined with phototherapy), T3 (AB-GG combined with phototherapy), and T4 (M-16V combined with Bb-12 combined with AB-GG combined with phototherapy).

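### The probiotic dose is given once as 10^9 CFU in 5 drops for all active arms, but the combination product is described as a powder package holding 10^9 of each of three strains, so what T4 receives is not fixed

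*Protocol article*

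**What the plan says.** Four places in the protocol article bear on what the combination arm receives.

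- **Study procedure** lists all five arms, including the one that takes all three probiotics, and then gives a single dose: "The probiotic dose is 10^9^ colony-forming units (5 drops) administered orally once daily for 1 month".
- **Abstract, Methods and analysis** puts the combination in the same list as the single strains: "to receive either 10^9^ colony-forming units of AB-GG, Bb-12, M-16V, a combination of the three probiotics with blue-light phototherapy".
- **Interventions, item 2** describes the combination product differently. It "contains Bifidobacterium breve 10^9^, Lactobacillus rhamnosus 10^9^ and Bifidobacterium animalis 10^9^ per package". The form is also different: "The aforementioned drugs are freeze-dried powder, stored at room temperature, with a 30-month shelf life". On administration it says: "The probiotics will be mixed into the milk and consumed once a day, with a treatment course lasting for one month".
- **Allocation concealment** defines the arm by its strains only, with no amount: "T4 (M-16V combined with Bb-12 combined with AB-GG combined with phototherapy".

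No section says whether 10^9 in T4 is a total or a per-strain figure, how many packages make up a day's dose, or how 5 drops relate to a package of powder. The limitations in the Discussion do not mention a dose difference between arms.

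**The concern.** The amount and the form of the T4 treatment can each be read in two ways from the current text. The two readings of the amount are different treatments.

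This matters for interpretation because the abstract states the aim as examining the three strains and also their combination. With three single-strain arms beside a combination arm, readers will set T4 against T1–T3. The Mann-Whitney and Kruskal-Wallis tests planned between groups leave room for that. What such a comparison means depends on the reading. Either T4 has the same total CFU as the other arms and less of each strain, or it has the same amount of each strain and a larger total.

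It also matters for describing the treatment. Table 1 schedules discharge on day 4 and the course runs for 30 days, so most doses fall after discharge. The unit dispensed, drops or package, should therefore be unambiguous.

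**Working it through.** The dose is a stated figure and not the output of a formula, so there is no calculation of the plan's to reproduce. The check puts the statements side by side and does the arithmetic under each reading.

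**Inputs**

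| Item | Value | Where |
|---|---|---|
| Daily dose, no arm singled out | 10^9 CFU, 5 drops, once daily | Study procedure |
| Dose with the combination in the list | 10^9 CFU | Abstract |
| Content of the combination package | 10^9 for each of 3 strains | Interventions |
| Form | freeze-dried powder, mixed into milk | Interventions |
| Infants in T4 | 20 of 100 | Randomization |

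**Assumptions the article does not state**

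- The package content is in CFU (Interventions gives no unit).
- One package is taken per day (inferred from once-daily use).
- Where a total is divided among strains, the split is equal.

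**Package content:** 3 strains × 10^9 = 3 × 10^9.

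**Reading A: 10^9 is the total in every probiotic arm** (the literal sense of the abstract and Study procedure).

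- T4 total = 10^9, and the ratio to a single-strain arm is 10^9 / 10^9 = 1.
- T4 per strain = 10^9 / 3 ≈ 3.3 × 10^8, one third of that strain's amount in its own arm.
- Share of a package = 10^9 / (3 × 10^9) = 1/3, so the daily dose does not match one package.

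**Reading B: 10^9 is per strain.**

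- T4 per strain = 10^9, which agrees with the package description.
- T4 total = 3 × 10^9, and the ratio to a single-strain arm is 3 × 10^9 / 10^9 = 3.

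**Form:** neither reading explains how 5 drops measure a powder. Reading B adds a further question: whether T4 takes 5 drops of a mixed product or 3 × 5 = 15 drops of three separate ones.

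**Which comparisons are touched:** C0 receives no probiotic, so a contrast of one probiotic arm with C0 compares that arm's preparation, whatever its dose, with none. Only T4 against T1, T2 or T3 has total dose and strain mix changing together, and only under Reading B. Under Reading A the total is equal and the amount per strain differs.

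**The case against.** The strongest reply is that nothing here is a proven contradiction. Study procedure does not name T4 or say that 10^9 is a total. Read per strain, it matches the package exactly, and the abstract is a condensed list. That stands, so a reader who infers that the two statements cannot both be true goes further than the text allows. But the per-strain reading does not close the matter. It makes T4's total three times that of the other arms if one package is taken daily, and the article never says so.

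Second, T4 against T1–T3 is not a named contrast. Purpose and hypothesis compares experimental with control, and Sample size rests on a two-sample comparison of 47% with 10%. That also stands. A reader might infer that a planned analysis is invalid, or that claims for T4 must be confined to T4 against C0. The document does not support either. With single-strain arms at one common dose, a combination arm can match the per-strain amount or the total, but not both. Either choice is legitimate, and comparing whole preparations is a valid question. What is needed is to state which was chosen and what follows from it.

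Third, the powder sentence in Interventions follows a description of the combination product only, so the drops might belong to another product. That is possible, but Study procedure gives drops as the measure of the probiotic dose without exception, and nothing assigns a form to each arm.

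Fourth, the full protocol may hold dispensing detail by arm. If so, the article need only be brought into line with it. The point rests on what the article prints in different places, and not on detail that it leaves out. It would likewise be speculation to infer that infants within T4 are actually receiving different amounts; the article gives no evidence of that.

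**Conclusion.** The point holds as an unreconciled statement of dose and form. On the literal reading, the abstract and Study procedure (10^9 CFU in total) conflict with Interventions (3 × 10^9 per package) by a factor of three for T4. On the per-strain reading the figures agree, and the factor of three moves to the comparison of T4's total CFU with that of each of T1–T3. Drops versus powder remains open on both. The threefold daily figure assumes one package a day and CFU as the package unit. The 3.3 × 10^8 per strain assumes an equal split.

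The reach is limited: 20 of 100 infants, and the interpretation of any comparison of T4 with a single strain. Sample size and the comparisons of each probiotic arm with C0 are not affected by the dose difference, although T4 still needs a defined treatment for its result to be described. It should be corrected, because it concerns what infants receive and what can be concluded about combining the strains.

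**What to change.** Reconcile the abstract (Methods and analysis), Interventions and Study procedure so that each of T1–T4 has one consistent statement of:

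1. CFU per strain per day,
2. total CFU per day,
3. the physical form and the measure dispensed (drops, package or other), including how many units make a daily dose.

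The sponsor decides which of the present statements is correct, after checking the dispensing records. This review takes no position on that.

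If T4's total CFU differs from that of T1–T3, add a sentence to the analysis or limitations text: a comparison of T4 with a single-strain arm compares whole preparations and cannot separate combining strains from total dose. No restriction is needed on the comparisons with C0.

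The cost is a protocol clarification, a records check and one sentence of interpretation. There are no extra patients, samples or analyses.
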